## 5.3 Study Treatment

After enrolment, patients in the study group (luspatercept arm) will be scheduled for luspatercept treatment. If the patients meet the inclusion criteria, they will receive luspatercept (0.7 to 1.4 mg/kg) subcutaneously. In cases of grade 3 or worse AEs (not including haematologic recovery), dose modifications, including dose reductions or interruptions, will be permitted at the discretion of the physician.

## 5.4 Follow-up

From the beginning of the first administration, the complete blood count will be monitored every 7 days within 20 days.

All the subjects will be followed for safety and tolerability within 20 days after luspatercept treatment. With the exception of haematologic AEs, all AEs will be graded according to the National Cancer Institute Common Toxicity Criteria version 5.0.

# 6. Efficacy Assessments

## 6.1 Definitions

- HI-E is defined as hematologic improvement-erythroid;
- HI-N is defined as a neutrophil count of < 1 × 10^9^/L at pretreatment and the achievement of an absolute neutrophil increase of ≥ 0.5 × 10^9^/L after treatment;
- HI-P is defined as a platelet increase of ≥ 30 × 10^9^/L among patients with pretreatment levels < 100 × 10^9^/L.

## 6.2 Primary Efficacy Endpoint

1. Hematologic improvement-erythroid (HI-E)

1. For patients requiring RBC transfusions before administration: the achievement of red blood cell transfusion independence (RBC-TI)
2. For RBC-TI patients at the first administration: mean Hb increase ≥ 1.5 g/dL

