# 3. Study Design

This is a prospective single-arm clinical study to evaluate luspatercept for promoting hematopoietic recovery in patients with poor hematopoietic reconstitution after allo-HSCT.

Patients with poor hematopoietic reconstitution after HSCT receiving luspatercept treatment will be enrolled, and the dose of luspatercept ranged from 0.7 to 1.4 mg/kg subcutaneously on the basis of routine supportive therapy. The complete blood count will be monitored every 7 days within 20 days from the beginning of luspatercept treatment. The primary endpoint was defined as hematologic improvement-erythroid (HI-E), which included the achievement of red blood cell transfusion independence (RBC-TI) for patients requiring RBC transfusions before administration, as well as a mean Hb increase ≥ 1.5 g/dL for RBC-TI patients at the first administration. The secondary endpoints included proportions of patients who achieved absolute increases in neutrophil ≥ 0.5 × 10^9^/L and platelet counts ≥ 30 × 10^9^/L, respectively; proportions of patients who achieved HI-neutrophil (HI-N) and HI-platelet (HI-P) counts; measurements of white blood cell (WBC), absolute neutrophil and platelet counts; and mean changes from baseline.

All the subjects will be followed for safety and tolerability within 20 days post-treatment. With the exception of haematologic adverse effects (AEs), all AEs will be graded according to the National Cancer Institute Common Toxicity Criteria version 5.0.

AEs= adverse effects; allo-HSCT= allogeneic hematopoietic stem cell transplantation; BM= bone marrow; EC= endothelial cell; HI-E= hematologic improvement-erythroid; HI-N= hematologic improvement-neutrophil; HI-P= hematologic improvement-platelet; MDS= myelodysplastic neoplasm; RBC-TI= red blood cell transfusion independence; TGF-β1= transforming growth factor-beta 1; WBC= white blood cell.

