## 6.4 Schedule and Methods of Efficacy Assessments

The patient's peripheral blood will be drawn to assess the recovery of WBC, ANC, Hb and platelets after the administration of luspatercept.

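### The haemoglobin limb of HI-E requires transfusion independence only at first dose, so a patient transfused later can count as a responder; the secondary platelet and neutrophil responses have a related gap

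*Protocol*

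**What the plan says.** Protocol section 6.2 builds HI-E from two limbs.

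- **Limb 1:** "For patients requiring RBC transfusions before administration: the achievement of red blood cell transfusion independence (RBC-TI").
- **Limb 2:** "For RBC-TI patients at the first administration: mean Hb increase" of at least 1.5 g/dL.

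The synopsis and sections 3 and 11.1.2 repeat the same two limbs. In limb 2 the transfusion condition applies at the first dose. Nothing requires the patient to stay transfusion-free, and nothing says how a haemoglobin value taken after a red cell transfusion is scored.

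Section 6.1 defines the secondary responses by a pretreatment threshold and the size of the rise. For neutrophils this is "the achievement of an absolute neutrophil increase of" 0.5 × 10^9/L or more from below 1 × 10^9/L. For platelets, "HI-P is defined as a platelet increase of" 30 × 10^9/L or more from below 100 × 10^9/L. Section 6.3 adds the same two rises without a pretreatment threshold. Section 6.4, on assessment methods, says only that "peripheral blood will be drawn to assess the recovery of WBC, ANC, Hb and platelets after the administration of luspatercept".

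Section 3 gives luspatercept "subcutaneously on the basis of routine supportive therapy" and does not itemise that therapy. The three exclusion criteria in section 4.1.3 do not mention growth factors.

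**The concern.** Followed literally, limb 2 can give the wrong answer. A patient who enters without needing red cells and then starts to need them has got worse. If transfusion lifts the mean haemoglobin by 1.5 g/dL, the rule still records an erythroid response.

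The trial has one arm and is sized against a fixed 14% (section 11.1.1). No concurrent control carries the same supportive-care effect, so such miscounts go straight into the observed rate. The gap between reference and target is 14 percentage points, about 9 responders in 64 (0.14 × 64 = 8.96), so a few miscounts matter.

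For the secondary endpoints, support given after dosing can create a platelet or neutrophil response. Support given before the baseline count can hide one, because it raises the starting value or moves the patient above the threshold of 100 or 1 × 10^9/L. Those results can be wrong in either direction.

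**Working it through.** **Inputs from the protocol (section 11.1.1).** Reference rate 14%, target 28%, type I error 5% with sidedness not stated, power 80%, 10% loss, N = 64. The synopsis specifies an intent-to-treat analysis, so 64 is used as the denominator.

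**The plan's own figure.** One-sample proportion, normal approximation, two-sided 5%:

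n = [1.96·√(0.14·0.86) + 0.842·√(0.28·0.72)]² / 0.14² = 57.1

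Allowing for 10% loss, 57.1/0.9 = 63.5, which rounds up to 64. The stated sample size reproduces, and the scoring change proposed here alters none of its inputs.

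**Success rule.** The protocol states no cut-off, so two were derived from exact binomial tails with N = 64 and p = 0.14:

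- At least 16 responders: P = 0.0135. This is the smallest cut-off with a tail of 2.5% or less.
- At least 15 responders: P = 0.0289. This is the smallest cut-off with a tail of 5% or less.

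The figures 1.4% and 2.9% are the exact sizes of these rules. The protocol's nominal level is 5%.

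**Effect of miscounting in limb 2.** Let f be the share of patients who are transfusion independent at first dose. Let t be the share of true non-responders among them who are scored as responders through transfusion. Limb 1 contributes nothing. With a true rate of 14% in both limbs:

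observed rate = 0.14 + f × 0.86 × t

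The documents give neither f nor t; every pair below is an assumption.

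| f | t | Observed rate | P(≥16 of 64) | P(≥15 of 64) |
|---|---|---|---|---|
| any | 0 | 14.0% | 1.4% | 2.9% |
| 20% | 5% | 14.9% | 2.3% | 4.6% |
| 20% | 10% | 15.7% | 3.7% | 6.9% |
| 50% | 5% | 16.2% | 4.5% | 8.3% |
| 50% | 10% | 18.3% | 11.3% | 18.2% |
| 50% | 20% | 22.6% | 36.9% | 48.5% |

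For example, f = 50% and t = 10% gives 0.14 + 0.5 × 0.86 × 0.10 = 0.183, or about 2.8 extra responders in 64 (0.043 × 64).

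**Secondary endpoints.** No reference rate is stated for these, so no comparable false-success figure can be computed.

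**The case against.** **Only part of the primary endpoint is exposed.** A reader might infer that transfusion can produce the primary result in any patient. Limb 1 rules that out, since a patient receiving red cells is not transfusion independent. Applying a contamination share to all non-responders would overstate the effect.

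**The word mean may protect limb 2.** With counts every 7 days within 20 days (section 5.4), one post-transfusion value averaged with the others may not reach 1.5 g/dL, and a transfusion that only restores a fallen haemoglobin adds nothing. This lowers the plausible t. It does not close the gap: the protocol does not say what the mean is taken over, and few values enter it.

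**The size is assumed.** This stands. At the low end, false success remains below the nominal 5%.

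**The 14% may contain the same effect.** It comes from a cited study that cannot be checked here. If that study also counted rises under supportive care, part of the bias is already in the reference. It would be too strong to say that an inactive drug will beat 14%.

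**Use of growth factor and platelet transfusion is inferred.** The protocol names neither. Red cell transfusion is better supported, because section 6.2 itself provides for patients who need it.

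**The error does not always favour the drug.** A reader might infer that it does. For platelets and neutrophils, support before baseline works the other way.

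**An analysis plan could settle this.** Handling of affected values is often placed there. But section 6.2 states the primary response rule itself, section 11.2.2.2 refers back to it as already described in detail, and that rule admits transfused patients. On data capture, section 14 already requires treatment results in the records and CRF, so the dates may partly exist.

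**Conclusion.** The point holds for limb 2 of HI-E, where the stated rule lets a newly transfused patient count as an erythroid responder. It holds with less weight for the secondary platelet and neutrophil responses, which affect no comparison with 14% and depend on an inference about what supportive therapy includes.

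The size is unknown. Over the scenarios shown, false success runs from 2.3–4.6% to 37–48%, depending on two shares the documents do not give and on cut-offs derived for this review. The calculation also assumes that the 14% reference is free of the same effect. The table shows what the rule permits and does not predict what will happen in this trial.

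Priority: must-fix for the primary haemoglobin limb, lower for the secondary endpoints.

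**What to change.** **Primary endpoint (section 6.2, and wherever it is repeated).** State that limb 2 counts as a response only if no red cell transfusion was given from first dose to the end of the 20-day window. Any red cell transfusion in that period is scored as non-response.

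**Secondary endpoints (sections 6.1 and 6.3).** Count baseline and post-dose platelet and neutrophil values only if they fall outside a prespecified interval after the last platelet transfusion or growth factor. The sponsor should choose the interval with the 7-day count schedule in mind. Score a patient with no qualifying post-dose value as a non-responder. Apply the same scoring rule to other blood-forming agents, whether started in the window or continued from baseline.

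**Data.** Record the dates of these treatments on the CRF.

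These are scoring rules only; they change no patient's care and leave N = 64 as it is. The cost is revised endpoint wording and a few CRF fields. Observed response rates may be lower, and some secondary values will be lost.

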## 6.3 Secondary Efficacy Endpoints

1. Hematologic improvement-leukocyte

1) Proportions of patients who achieved absolute increases in neutrophil ≥ 0.5 × 10^9^/L;

2) Proportions of patients who achieved HI-neutrophil (HI-N);

3) Measurements of white blood cell (WBC), absolute neutrophil and mean changes from baseline.

2. Hematologic improvement-platelet

1) Proportions of patients who achieved absolute increases in platelet counts ≥ 30 × 10^9^/L;

2) Proportions of patients who achieved HI-platelet (HI-P);

3) Measurements of platelet counts and mean changes from baseline.

## 6.4 Schedule and Methods of Efficacy Assessments

The patient's peripheral blood will be drawn to assess the recovery of WBC, ANC, Hb and platelets after the administration of luspatercept.

# 7. Safety Evaluation

All the subjects enrolled in the study will be evaluated for safety and tolerability. Safety and tolerability will be assessed by the incidence and severity of AEs and changes from baseline of all relevant parameters, including laboratory test values, physical examination findings, vital signs, and ECOG performance scores. With the exception of haematologic AEs, all AEs will be graded according to the National Cancer Institute Common Toxicity Criteria version 5.0.

### 7.1 Medical History

Each subject's medical history will be obtained at screening. Information on any prior or existing medical conditions will be recorded on the appropriate CRF.

### 7.2 Vital Signs and Physical Examination

Vital signs and physical examination results must be documented before randomization, once a week after enrolment. The next 8 steps must be performed:

⚫ Physical examination

⚫ Heart rate

⚫ Blood pressure

⚫ Body temperature

⚫ Rate of respiration

⚫ Body weight

⚫ ECOG performance status

⚫ Signs of infection

### 7.3 Clinical Symptoms

During the study, the patients' clinical symptoms must be documented. The clinical symptoms may be associated with the administration of luspatercept reported previously.

### 7.4 Clinical Laboratory Evaluations

Before initiation of the study, the monitors will document the normal range of each test in every involved laboratory. During the study, the following steps will be performed:

⚫ Routine blood: white cell counts, neutrophil cell counts, hemoglobin, and platelet counts

⚫ Hepatic function: total bilirubin (both direct bilirubin and indirect bilirubin must be documented when total bilirubin is elevated), ALT, AST, lactic dehydrogenase, alkaline phosphatase, albumin and total protein

- Renal function: serum creatinine, urea nitrogen and uric acid
- Other biochemical indicators: amylase and lipase
- Electrolytes: sodium, potassium, calcium and magnesium
- Coagulation function: prothrombin time, prothrombin time-international normalized ratio, activated partial thromboplastin time and fibrinogen
- Urinalysis: protein, glucose and erythrocyte
- Electrocardiogram
- Chest imaging examination

## 8 Adverse Events and Serious Adverse Events (SAEs)

The investigator is responsible for detecting, documenting and reporting events that meet the definition of an AE or SAE.

### 8.1. Definitions

## 8.1.1 Adverse Events

An AE is any untowards medical occurrence in a subject of a clinical investigation, which does not necessarily have a causal relationship with the medicinal product. Therefore, an AE can be any unfavourable and unintended sign, including an abnormal laboratory finding, symptom, or disease (new or exacerbated), whether or not it is considered to be related to the product. This definition includes any newly occurring event or previous condition that has increased in severity or frequency since the administration of the product. However, haematologic recovery or death due to persistent nonremission should not be recorded as AEs.

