**Date of Signature 2022-09-05**

**Institution/Affiliation Peking University People’s Hospital**

**City, Province, Country Beijing, China**

# Study Synopsis

| **Study title** | Luspatercept for promoting hematopoietic recovery in patients with poor hematopoietic reconstitution after allogeneic hematopoietic stem cell transplantation——a prospective single-arm clinical study |
| --- | --- |
| **Indication** | Poor hematopoietic reconstitution after allogeneic hematopoietic stem cell transplantation |
| **Study applicant** | Peking University People’s Hospital |
| **Study center** | Peking University People’s Hospital |
| **Number of subjects planned** | Approximately 64 subjects |
| **Study duration** | Estimated to be 3 year |
| **Objectives** | **Primary objective:**  To evaluate the efficacy and safety of luspatercept for promoting hematopoiesis recovery in patients with poor hematopoietic reconstitution after allogeneic hematopoietic stem cell transplantation (allo-HSCT).  **Exploratory objectives:**  To evaluate the influence of luspatercept in the bone marrow microenvironment among patients with poor hematopoietic reconstitution after allo-HSCT. |
| **Study design** | This is a prospective single-arm clinical study to evaluate luspatercept for promoting hematopoietic recovery in patients with poor hematopoietic reconstitution after allo-HSCT.  Approximately 64 subjects will receive luspatercept treatment.  The dose of luspatercept ranged from 0.7 to 1.4 mg/kg subcutaneously on the basis of routine supportive therapy.  The complete blood count will be monitored every 7 days within 20 days from the beginning of luspatercept treatment.  Adverse events were evaluated following the National Cancer Institute Common Toxicity Criteria version 5.0. |
| **Inclusion criteria** | Subjects eligible for enrolment in this study must meet all of the following criteria:   1. Poor hematopoietic reconstitution after HSCT receiving luspatercept treatment 2. Aged 18-60 years 3. Comply with the study and follow-up procedures |
| **Exclusion criteria** | Subjects meeting any of the following criteria are ineligible for this study:   1. Severe organ injury 2. Uncontrolled active infections 3. Hypersensitivity to luspatercept |

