## 8.1.2 Serious Adverse Events

A serious adverse event is any untowards medical occurrence that, at any dose:

- - Results in death
  - Is life-threatening
  - Requires hospitalization or prolongation of existing hospitalization—i.e., the AE requires at least a 24-hour inpatient hospitalization or prolongs a hospitalization beyond the expected length of stay.

Hospitalization or prolongation of existing hospitalization for social reasons will not be reported as an SAE.

- - Results in disability/incapacity
  - Results in congenital anomalies/birth defects
  - Important medical events

Medical or scientific judgement should be exercised in deciding whether SAE reporting is appropriate in other situations. An important medical event is an event that may not result in death, be life-threatening, or require hospitalization but is clearly of major clinical importance. The AE may jeopardize the subject or require intervention to prevent a serious outcome.

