## 8.2 Assessment of Severity

With the exception of hematologic AEs, all AEs will be graded according to the National Cancer Institute Common Toxicity Criteria version 5.0. When the National Cancer Institute Common Toxicity Criteria version 5.0 criteria do not apply, severity will be defined according to the following criteria:

| **Severity** | **Description** |
| --- | --- |
| Grade 1- Mild | Asymptomatic or mild symptoms; clinical or diagnostic observations only; intervention not indicated |
| Grade 2- Moderate | Minimal, local or noninvasive intervention indicated; limiting age-appropriate instrumental activities of daily living (ADL) |
| Grade 3- Severe | Medically significant but not immediately life threatening; hospitalization or prolongation of hospitalization indicated; disabling; limiting self-case ADL |
| Grade 4- Life-threatening | Life-threatening consequences; urgent intervention indicated |
| Grade 5- Death | Death |

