## 8.4 Recording and Reporting of AEs and SAEs

All AEs and SAEs must be recorded in the appropriate CRF, regardless of whether they are causally related to the study treatment. Each SAE must be reported promptly on the Serious Adverse Event Report Form and submitted to the Independent Ethics Committee within 24 hours by the investigator. The information recorded on the Serious Adverse Event Report Form will include at least the following: subject number, identity of the event, study drug name and dose, investigator's assessment of the event's severity and relationship to study treatment, and investigator's name and signature. When examining original medical records, clinical monitors must collect and verify detailed information on AEs and SAEs. All AEs and SAEs should be followed up until they are resolved.

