### 11.2.2.3 Analysis of Safety

Safety and tolerability will be assessed by the incidence and severity of AEs and changes from baseline of all relevant parameters, including laboratory test values, physical examination findings, vital signs, and ECOG performance scores. The definition of AEs has been detailed in previous section. With the exception of haematologic AEs, all AEs will be graded according to the National Cancer Institute Common Toxicity Criteria version 5.0. All subjects will be monitored for AEs within 20 days post-treatment. Categorical data will be summarized by the proportion of total subjects. Quantitative data will be described using arithmetic averages or medians for central tendencies and standard deviations or interquartile ranges for distribution ranges.

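### Section 8.1.1 bars deaths attributed to an undefined persistent nonremission from the AE record, which contradicts the SAE rules in 8.1.2 and 8.4

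*Protocol*

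**What the plan says.** Section 8.1.1 defines an AE broadly: any untoward occurrence, related to the product or not, including abnormal laboratory findings and the worsening of an existing condition. Its last sentence then makes an exception: "haematologic recovery or death due to persistent nonremission should not be recorded as AEs".

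Section 8.1.2 lists "Results in death" as the first criterion for an SAE and makes no exception. Section 8.4 adds "All AEs and SAEs must be recorded in the appropriate CRF, regardless of whether they are causally related to the study treatment", and requires each SAE report to be "submitted to the Independent Ethics Committee within 24 hours by the investigator". Neither section repeats the exception or refers back to it.

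On grading, the study design row of the synopsis says "Adverse events were evaluated following the National Cancer Institute Common Toxicity Criteria version 5.0", without qualification. Section 8.2 says "With the exception of hematologic AEs, all AEs will be graded according to the National Cancer Institute Common Toxicity Criteria version 5.0", then gives a generic grade 1 to 5 scale for cases that the NCI criteria do not fit. The same exception for haematologic AEs stands in the safety paragraph of the synopsis and in sections 3, 5.4, 7 and 11.2.2.3.

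**The concern.** Site staff cannot obey both 8.1.1 and 8.4 for the same death. Which one they follow decides whether that death is in the safety data.

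Section 2.1 puts safety alongside efficacy in the primary objective, and sections 7 and 11.2.2.3 assess it through AE incidence and severity plus changes from baseline. Section 6 names no mortality endpoint that would pick up a death missing from the AE data. Section 5.2 makes the study open-label, so the person deciding that a death belongs to the excluded category knows the treatment. With no control arm, there is no comparison in which a tendency to attribute deaths this way would show. An error of this kind can only make the drug look safer.

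**Working it through.** The protocol states no figure on this point, so the check is a comparison of text followed by a simple proportion.

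**Step 1. Follow one death through the rules.** Suppose a patient dies during follow-up and the investigator attributes the death to persistent nonremission.

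| Section | Rule | Result for this death |
|---|---|---|
| 8.1.1, definition | "This definition includes any newly occurring event or previous condition that has increased in severity or frequency since the administration of the product" | Is an AE |
| 8.1.1, last sentence | Exception for this cause of death | Not recorded as an AE |
| 8.1.2 | Fatal outcome is an SAE criterion, no exception | Is an SAE |
| 8.2 | Grade 5 is death | Has a grade |
| 8.4 | All AEs and SAEs recorded, whatever the causality | Entered in the CRF |
| 8.4 | Each SAE to the ethics committee within 24 hours | Reported |

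Only the last sentence of 8.1.1 points the other way.

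**Step 2. Can the sections be read together?** One could say that such a death is an SAE without being an AE. That does not work well: 8.1.2 builds the SAE on the same basic concept as 8.1.1 and itself calls the event an AE when it explains hospitalization and important medical events. Even on that reading, the safety analysis in 7 and 11.2.2.3 is of AEs, so the death would still fall outside AE incidence.

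**Step 3. What does the excluded category cover?** The term occurs only in 8.1.1. Remission is not an endpoint in 6.2 or 6.3. It could mean persistence of the underlying disease or failure of the blood counts to recover; the protocol does not say which. Section 8.3 already provides causality categories for events thought unrelated to the drug, so attribution can be recorded without removing the death.

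**Step 4. Size.** Input: 64 planned patients (4.1.1, 11.1.1). Effect on the fatal-AE proportion of k omitted deaths = k/64.

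- k = 1: 1/64 = 1.6 percentage points
- k = 2: 2/64 = 3.1
- k = 3: 3/64 = 4.7
- k = 6: 6/64 = 9.4

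These values of k are assumptions to show scale. For k = 3, the exact (Clopper-Pearson) 95% interval for 3/64 is 1.0% to 13.1%. With the three omitted, 0/64 would be reported with upper limit 1 − 0.025^(1/64) = 5.6%.

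**Step 5. Grading of haematologic AEs.** The synopsis design row applies the NCI criteria to adverse events without exception; the synopsis safety paragraph and sections 3, 5.4, 7, 8.2 and 11.2.2.3 except haematologic AEs. The generic scale in 8.2 may cover the excepted events, but 8.2 does not say so. Nothing in these sections stops haematologic AEs from being recorded. Section 7.4 collects the counts, sections 7 and 11.2.2.3 summarise laboratory changes from baseline, and 6.3 lists mean changes in white cells, neutrophils and platelets.

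**The case against.** The strongest reply is that this is a wording slip with no shown effect. Safety follow-up is 20 days, which limits how many such deaths can arise. The term may mean only relapse or persistence of the underlying malignancy, which many would treat as disease outcome and not drug harm. Nothing forbids a separate count of deaths, and the analysis plan, which is not shown, may contain one. The primary HI-E analysis and the sample size are untouched.

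Much of this is fair on size, and no expected number of deaths can be claimed. It does not remove the contradiction. An analysis plan can summarise only what was collected, and 8.1.1 governs collection. If the term was meant narrowly, the protocol does not say so.

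A reader might infer more than the text supports:

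- That haematologic AEs go ungraded altogether. The exception is from the NCI criteria only, and the generic scale in 8.2 may apply.
- That falls in counts are invisible because the endpoints count only improvement. Mean changes from baseline would show falls, and laboratory changes are a safety measure.
- That the grading exception also breaches the SAE rules. It does not; only the death clause conflicts with 8.1.2 and 8.4.
- That the trial drops the deaths most relevant to graft failure. The protocol does not use that term, one category of death is excluded, and its meaning is open. A fatal infection or bleed would be a new event in its own right under 8.1.1.
- That the termination reasons in 9.2 are undermined. The death-based reason there concerns treatment-related death, and a death attributed to nonremission would not normally count towards it even if recorded. The link is weak.

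**Conclusion.** The point holds for deaths. Section 8.1.1 contradicts 8.1.2 and 8.4 on whether a death attributed to persistent nonremission is recorded, and the deciding term is undefined. If 8.1.1 is followed, deaths can be left out of half of the primary objective on an unblinded attribution, at 1.6 percentage points each. That figure assumes that all 64 planned patients form the safety denominator. The total effect cannot be stated because the protocol gives no expected number of such deaths; three is only an illustration. The contradiction does not depend on any count, and it should be corrected.

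The grading matter is secondary. The protocol is inconsistent between the synopsis design row and the rest, and silent on whether the generic scale covers haematologic AEs. Those events and the count changes remain in the data, so grading is unclear and not lost.

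**What to change.** - In 8.1.1, strike the words that exclude death due to persistent nonremission, so that the section agrees with 8.1.2 and 8.4.
- Record every death during follow-up as an SAE, with its cause and the causality assessment of 8.3.
- Report all-cause deaths in the safety results, with cause listed, so that readers can judge attribution for themselves.
- Reconcile the synopsis design row with the synopsis safety paragraph and sections 3, 5.4, 7, 8.2 and 11.2.2.3 on the grading of haematologic AEs, and state in 8.2 whether the generic scale applies to them. A table of shifts from each patient's baseline grade would be one way to present these events, but it is a preference and is not needed to resolve the inconsistency.

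The cost is protocol and CRF wording, a count of deaths, and a reported event rate that may look less favourable. The sample size and the primary efficacy analysis do not change.
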